**Methods:**

This prospective, multicenter cohort study plans to enroll 2000 patients with AIS within 14 days of symptom onset from 30 hospitals across China. Eligible patients will be followed up for 6 months after initiating medication treatments. The primary outcome will be the change in the National Institute of Health Stroke Scale score from baseline to outpatient follow-up. The secondary outcomes include overall mortality, stroke recurrence, new-onset major vascular events, global disability, and improvement of traditional Chinese medicine syndrome in 6 months. Adverse events or clinically significant changes in vital signs and laboratory parameters, regardless of the severity, will be recorded during the trial to assess the safety of DZHJTI. An augmented inverse propensity weighted estimator will be used to reduce variability and improve accuracy in average treatment effects estimation.

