**Secondary outcomes**		
	Overall mortality	—^b^
	Stroke recurrence	—
	New-onset major vascular events	Major adverse vascular events include ischemic stroke, hemorrhagic stroke, transient ischemic attack, myocardial infarction, and vascular-related death
	Global disability	Measured by BI^c^ and mRS^d^ scale
	improvement of TCM^e^ syndrome	Measured by TCM questionnaire
	Adverse events	Undesirable experiences occurring to participants during the trial are considered to be related to the DJHJTIf

^a^NIHSS: National Institute of Health Stroke Scale.

^b^Not available.

^c^BI: Barthel Index.

^d^mRS: modified Rankin Scale.

^e^TCM: traditional Chinese medicine.

^f^DZHJTI: Dazhu hongjingtian injection.

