### Sample Size

According to the previous studies, the ineffective rate assessed by NIHSS score (percentage of patients experiencing no change and deterioration) in controls was 8.75% (7/80), and the ratio of cases to controls was 0.31 [14]. To test the hypothesis that adjuvant treatment with DZHJTI significantly reduces the ineffective rate with a 2-sided α of .05, power of 0.80, and a 20% (n=248) dropout rate, a sample size of 619 cases in each group is required. Nevertheless, a sufficiently large sample size is also necessary to reduce the bias in real-world studies. Therefore, a total of 1000 case participants per group will be included.

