### Statistical Analysis

A statistical analysis plan was developed prior to initiating the cohort study. Continuous data will be summarized using mean, median, standard deviation, or IQR, while categorical data will be presented as counts and percentages. Between-group comparisons will be conducted using appropriate parametric tests (such as the 2-tailed Student *t* test) or nonparametric tests (such as the chi-square test, Fisher exact test, or Mann-Whitney *U* test). Time-to-event analysis will involve censoring patients at their last follow-up assessment when experiencing a clinical event, at the end of the study, or at the time of withdrawal from the study. Cumulative clinical events will be reported as Kaplan-Meier estimates. Hazard ratios will be calculated at 95% CIs using Cox proportional hazard regression methods.

During data analysis, both confounding factors and missing values will be taken into account. The augmented inverse propensity weighted (AIPW) estimator will be used to obtain a marginal estimate of the treatment effect rather than a conditional estimate. AIPW analysis creates a pseudopopulation in which the relationship between the confounders and the exposure is blocked. Multiple imputation will be used to handle missing values of covariates, and both complete case and imputed data sets will be analyzed. For each imputed data set, the AIPW estimator will be used to estimate the treatment effect, and Rubin rules will be used to combine these estimates and obtain an overall estimate [20]. Sensitivity analyses for unmeasured confounding in observational studies will be performed using the methodology proposed by VanderWeele and Ding [21]. All statistical tests will be 2-sided with statistical significance set at *P*<.05. Statistical analyses will be conducted using SAS software (version 9.4; SAS Institute Inc).

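### Kaplan-Meier is named for all cumulative clinical events, so the 6-month risks of stroke recurrence and major vascular events will be slightly overstated when patients die of a competing cause first

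*Protocol article*

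**What the plan says.** Three parts of the protocol article bear on this point.

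- **Outcomes.** The abstract lists mortality, recurrence and vascular events as separate outcomes over 6 months: "The secondary outcomes include overall mortality, stroke recurrence, new-onset major vascular events, global disability, and improvement of traditional Chinese medicine syndrome in 6 months". Table 2 gives stroke recurrence no definition that includes death. It defines the composite thus: "Major adverse vascular events include ischemic stroke, hemorrhagic stroke, transient ischemic attack, myocardial infarction, and vascular-related death". Non-vascular death is outside both.
- **Estimator.** The Statistical Analysis section states "Cumulative clinical events will be reported as Kaplan-Meier estimates", with no exception by outcome. The comparative measure follows: "Hazard ratios will be calculated at 95% CIs using Cox proportional hazard regression methods".
- **Censoring.** The same section says "Time-to-event analysis will involve censoring patients at their last follow-up assessment when experiencing a clinical event, at the end of the study", and adds withdrawal from the study. Death is not given a status of its own, and no competing-risk method appears anywhere in the article.

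**The concern.** Kaplan-Meier has two states, event and censored. It treats a censored patient as still able to have the event, at the rate seen in those who remain under observation. That is reasonable for withdrawal or the end of follow-up, but not for a patient who has died. With deaths censored, one minus Kaplan-Meier estimates the risk in a hypothetical population in which nobody dies of the competing cause. The article's stated objective is effectiveness in real-world clinical settings, where the relevant quantity is the proportion of patients who actually have the event.

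Deaths have to be expected: patients enter in the acute phase, those with an NIHSS score of 0-5 are excluded, follow-up lasts 6 months, and mortality is itself an outcome. The published 6-month risks of recurrence and of major vascular events would then be somewhat too high. They would also not match the event counts, even with no loss to follow-up. Treatment is chosen by the physician, so competing mortality may differ between groups, and the overstatement could then differ too.

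**Working it through.** The article states no event rate, death rate or event count for these outcomes, so there is no figure of its own to reproduce. The direction needs no outside figure. The size is shown over an assumed range.

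**Inputs**
- Horizon: 6 months (abstract, Methods).
- F1, the true proportion with the event by 6 months: 5% and 10% (assumed).
- F2, the proportion dying of a competing cause before the event: 2%, 5%, 10% and 15% (assumed).

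**Formulas**, with constant cause-specific hazards over the 6 months:
- Total cumulative hazard: H = -ln(1 - F1 - F2)
- Share for the event: h1 = H × F1 / (F1 + F2)
- What Kaplan-Meier targets when competing deaths are censored: 1 - exp(-h1)
- Upper bound, if every competing death precedes every event: F1 / (1 - F2)

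**One case in full.** F1 = 10%, F2 = 10%: H = -ln(0.80) = 0.2231; h1 = 0.2231 × 0.5 = 0.1116; 1 - exp(-0.1116) = 10.56%. The excess is 0.56 points, or 5.6% relative. The upper bound is 0.10 / 0.90 = 11.11%.

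| True risk F1 | Competing death F2 | 1 - KM, constant hazards | Excess (points) | Relative excess | 1 - KM, all deaths first |
|---|---|---|---|---|---|
| 5% | 2% | 5.05% | 0.05 | 1.0% | 5.10% |
| 5% | 5% | 5.13% | 0.13 | 2.6% | 5.26% |
| 5% | 10% | 5.27% | 0.27 | 5.5% | 5.56% |
| 5% | 15% | 5.43% | 0.43 | 8.5% | 5.88% |
| 10% | 2% | 10.10% | 0.10 | 1.0% | 10.20% |
| 10% | 5% | 10.27% | 0.27 | 2.7% | 10.53% |
| 10% | 10% | 10.56% | 0.56 | 5.6% | 11.11% |
| 10% | 15% | 10.87% | 0.87 | 8.7% | 11.76% |

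For the composite, vascular-related death counts as an event and only non-vascular death competes, so the rows with small F2 apply. For recurrence, a death that follows a recurrent stroke does not compete, so F2 is below all-cause mortality.

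**Between groups.** Now hold the recurrence hazard equal in both groups, at a level that gives one minus Kaplan-Meier of 10.0% in each. Let m be the 6-month death risk that the competing-death hazard alone would give. The cumulative incidence at constant hazards is h1 / (h1 + h2) × [1 - 0.90 × (1 - m)], where h1 = -ln(0.90) and h2 = -ln(1 - m). This gives 9.75% at m = 5%, 9.50% at m = 10% and 9.24% at m = 15%.
- Mortality of 5% against 10%: Kaplan-Meier shows no difference; the true difference is 9.75 - 9.50 = 0.25 points.
- Mortality of 5% against 15%: 9.75 - 9.24 = 0.51 points. If 60% of the death hazard falls in the first month, it is 9.64 - 8.92 = 0.72 points.

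**Sampling error for scale.** The Sample Size section plans 1000 per group. At a 10% risk the 95% half-width is 1.96 × √(0.10 × 0.90 / 1000) = 1.9 points for one group and 1.96 × √(2 × 0.10 × 0.90 / 1000) = 2.6 points for the difference, before dropout or weighting.

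**The case against.** Four points can be made on the other side.

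1. **The analysis plan may settle it.** The article says that a statistical analysis plan exists, and it never says in so many words that deaths are censored. It is right that censoring of deaths is an inference. But the estimator is stated, for all clinical events, and the usual application of Kaplan-Meier leaves no other place for a death that is not itself the event. Counting such deaths as events would contradict Table 2. Keeping the dead at risk until 6 months would avoid the bias, but nothing in the article suggests it. The point is therefore about a stated method and not about missing detail.

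2. **The treatment effect does not rest on this estimate.** The comparative measure is the Cox hazard ratio. This stands: with deaths censored, it is interpretable as a cause-specific hazard ratio. A reader might infer that the hazard ratios are invalid. They are not; they need only the right label.

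3. **The bias is small beside sampling error.** This also stands. A reader might infer that the comparison between groups is seriously distorted. That would need competing mortality to differ by group, which the article gives no reason to assume, and even a threefold difference moves the contrast by well under one point.

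4. **Mortality may be low.** Textbox 1 also excludes severe cardiac insufficiency, renal insufficiency, dementia, hemorrhage after infarction and prior dependence. It admits patients up to 14 days after onset, so some of the earliest deaths may precede enrolment. This argues for the lower rows of F2 and against scenarios with many early deaths. It reduces the size and leaves the direction unchanged.

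**Conclusion.** The point holds as a minor correction to the reporting of two secondary outcomes. With competing deaths censored, one minus Kaplan-Meier is above the 6-month proportion of patients with the event whenever such a death occurs while events can still follow. Across the assumed range the excess runs from 0.05 to 0.87 points at constant hazards, with an extreme of 1.76 points if all deaths come first; it is probably below one point. Any between-group distortion is likely a fraction of a point.

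The conclusion rests on two assumptions: that deaths outside the outcome definition are censored, and that event and death rates lie in the ranges shown. The article cannot confirm either. A reader might also infer that the article already publishes inflated 6-month proportions. It publishes none; the point concerns what will be reported. Overall mortality, for which Kaplan-Meier is right, and the primary NIHSS outcome are not affected.

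**What to change.** In the Statistical Analysis section:

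- Keep Kaplan-Meier for overall mortality.
- For stroke recurrence, report the Aalen-Johansen cumulative incidence by group, with all-cause death before recurrence as the competing event.
- For new-onset major vascular events, report it with non-vascular death as the competing event.
- Keep the Cox model and label its hazard ratios for these two outcomes as cause-specific.
- Reword the censoring sentence at the same time. Read literally, it censors patients when they have a clinical event, and it should say how death is handled for each outcome.

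The cost is a change of wording. Follow-Up Procedures already has deaths confirmed by certificate, the composite already requires deaths to be classed as vascular or not, and SAS 9.4, the named software, can produce the estimate. The only downside is that the reported event proportions become slightly lower.

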### Treatment Regimens

All patients will receive current guideline-recommended treatments according to *Chinese Guidelines for the Diagnosis and Treatment of Acute Ischemic Stroke 2018* [15]. The most commonly used medications and treatments include intravenous thrombolysis drugs, antiplatelets, anticoagulants, drugs for volume expansion, neuroprotectants, medicines for improving cerebral blood flow, and traditional Chinese medicine. Cases will be recruited from patients who receive DZHJTI according to the physician’s order. The DZHJTI will be manufactured and supplied by Tonghua Yusheng Pharmaceutical Co, Ltd (approvals Z20060361 and Z20060362), with identical appearance, color, and flavor. The fingerprint-based quality control and ingredient identification met the Chinese pharmacopeia’s reference requirements (detailed information is provided in Multimedia Appendix 1). The administration and dosage of DZHJTI will be determined by the attending physicians based on the patients’ medical history and clinical manifestations.

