## Discussion

We present the rationale and design of a prospective, multicenter observational study that aims to evaluate the clinical effectiveness and safety of DZHJTI in the treatment of AIS in real-world settings. Rhodiola has long been used in Eurasian traditional medicine as a natural tonic, but DZHJTI’s efficiency in treating AIS is not well known because previous studies had limited external validity [22,23]. Thus, it is necessary to collect large longitudinal data to confirm the practical benefits and disadvantages of DZHJTI treatment in patients with stroke. These data can then be used to develop initiatives to improve evidence-based care and patient outcomes.

Adjuvant treatment with DZHJTI has been shown to have an additional positive effect on improving clinical symptoms and hemodynamic indexes in patients with AIS [14,24]. This beneficial effect may be attributed to the ability of its ingredients, including salidroside, tyrosol, and *Rhodiola* polysaccharide, and the fact that it contains flavonoids, phenolic compounds, trace elements, and amino acids. This has been demonstrated to activate antioxidant enzymes’ activity in brain tissue, reduce the oxidative damage of free radicals to cells, and improve glucose and lipid metabolism [25,26]. However, the evidence for the effectiveness of DZHJTI is still limited due to a lack of large controlled studies, and the strict treatment regimes in randomized controlled trials may be not applicable in clinical practice [14]. Therefore, well-designed prospective real-world studies with large sample sizes are necessary to evaluate the evidence.

Our study uses an observational design, and the treatments will not be specified by the study protocol. This approach has the advantage of reflecting real-world clinical practice, including therapy switches and concomitant medications, which can provide valuable insights into treatment effectiveness in diverse patient populations. Additionally, studying how DZHJTI is prescribed by health care providers and used in everyday environments can offer valuable information about the people and settings that are often underrepresented in randomized controlled trials, potentially leading to improvements in the way medicines are prescribed and used among these patient populations.

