However, it is important to note that biases are common in real-world studies. Participants from different study sites may differ in characteristics, and combined treatments can vary widely. Additionally, incomplete data can be a significant issue with real-world data sources. Therefore, we plan to use the AIPW estimator, which involves a doubly robust procedure to minimize bias if either the treatment or outcome model is correctly specified [27]. The accuracy of the AIPW estimator for the average treatment effect has been demonstrated under different scenarios of misspecification [27]. To perform propensity score analysis when data are missing, we will conduct the analysis in each imputed data set and then combine the estimates of the treatment effect to obtain an overall estimate. This method has been demonstrated to be unbiased under a missing at random mechanism, and Rubin rules have been shown to provide reliable variance estimates and show good balancing properties [20].

Another key consideration in this trial is selecting an appropriate primary outcome, which depends largely on the disease and should reflect the treatment effect and expected mechanism. NIHSS is a tool used to objectively quantify neurological impairment after stroke [28], while the modified Rankin Scale and modified Barthel Index are commonly used scales to measure disability or dependence in daily activities in patients with stroke or other neurological dysfunction [29]. Previous studies on herbal injection often have limited follow-up periods of up to 3 months due to drug metabolism. However, since AIS neurological function recovery is a slow process, with the main recovery period occurring within 2 to 6 months after onset [30], we evaluated the effects of DZHJTI on neurological recovery for a period of 6 months after discharge from the hospital.

To our knowledge, this is the first and largest prospective cohort study in China that evaluates the real-world effectiveness and safety of DZHJTI in the treatment of AIS. It may provide additional clinical evidence, including the duration of response, long-term drug effectiveness, and subgroup efficacy data of DZHJTI treatment for patients with AIS under the influence of other confounding factors. Ultimately, the results of this study will help optimize individualized interventions with DZHJTI for the treatment of AIS in China, leading to better patient outcomes and more standardized treatment practices.

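### The Kaplan-Meier and Cox analyses of event outcomes have no stated link to the confounding adjustment, and Kaplan-Meier is named for events that death can preclude

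*Protocol article*

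**What the plan says.** Treatment Regimens describes how the exposed group arises: "Cases will be recruited from patients who receive DZHJTI according to the" physician's order. The Discussion confirms it: "Our study uses an observational design, and the treatments will not be specified by the study protocol". It also warns that "Participants from different study sites may differ in characteristics, and combined treatments can vary widely".

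The first paragraph of Statistical Analysis sets out the group comparisons. "Between-group comparisons will be conducted using appropriate parametric tests" or nonparametric ones. For time-to-event outcomes, "Cumulative clinical events will be reported as Kaplan-Meier estimates", and "Hazard ratios will be calculated at 95% CIs using Cox proportional hazard regression methods". That paragraph mentions no weight, covariate or propensity score.

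The second paragraph turns to confounding: "During data analysis, both confounding factors and missing values will be taken into account". It then says: "The augmented inverse propensity weighted (AIPW) estimator will be used to obtain a marginal estimate of the treatment effect rather than a conditional estimate". It adds multiple imputation of covariates and a sensitivity analysis for unmeasured confounding. The section also says that a statistical analysis plan was written before the study began; that plan is not shown.

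The event outcomes (overall mortality, stroke recurrence and new-onset major vascular events) are secondary outcomes in the Abstract and Table 2. Mortality and vascular events also appear in the Objective's statement of the primary aim.

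**The concern.** When physicians decide who receives a drug, the treated and untreated differ in prognosis before treatment starts. A hazard ratio or pair of survival curves that ignores this mixes prescribing selection with drug effect. The article recognises the problem and names a remedy, but that remedy targets a different quantity from the two it names for event outcomes. A reader cannot tell whether the hazard ratios for mortality, recurrence and vascular events will be adjusted, or which estimate carries the inference if both a Cox and an AIPW result are reported.

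The second issue is the choice of Kaplan-Meier for cumulative events. A patient who dies can no longer have a recurrent stroke. Treating that death as ordinary censoring estimates the risk in a setting where nobody dies of anything else, which is higher than the risk patients actually face.

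At stake is whether an apparent benefit or harm on these outcomes, tested at P<.05, can be read as an effect of the drug.

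**Working it through.** The document gives no event count, event rate, hazard ratio or power for any time-to-event outcome, so there is no figure of its own to reproduce. The check is mainly one of wording, with illustrations on assumed inputs.

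**1. Does the named adjustment reach the named analyses?**

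| Element | Stated in the article | What it produces |
|---|---|---|
| Kaplan-Meier | Statistical Analysis, first paragraph; no weights named | A survival or cumulative event curve for each group |
| Cox model | Same paragraph; no covariates or weights named | A hazard ratio |
| AIPW | Statistical Analysis, second paragraph; Abstract; Discussion | A marginal average treatment effect |

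No sentence joins the third row to the first two, and none excludes event outcomes from adjustment. AIPW as described gives neither a curve nor a hazard ratio. It could give adjusted 6-month risks, but the article does not say that it will.

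**2. What an unadjusted comparison would do (assumed inputs).** Let a share p1 of DZHJTI patients and p0 of controls have severe stroke, let severity multiply the hazard by g, and let the drug have no effect. The unadjusted ratio is then approximately

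(1 + p1(g − 1)) / (1 + p0(g − 1)).

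With two groups of equal size, SE(log HR) ≈ 2/√(events). The two-sided rejection probability follows from the normal distribution at ±1.96.

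- p1 = 0.30, p0 = 0.45, g = 3: 1.60/1.90 = 0.84. The log is −0.172. With 100 events SE = 0.200 and the rejection probability is about 14%; with 200 events SE = 0.141 and it is about 23%.
- p1 = 0.35, p0 = 0.45, g = 3: 1.70/1.90 = 0.89. Rejection is about 9% with 100 events and 12% with 200.
- p1 = 0.35, p0 = 0.40, g = 2: 1.35/1.40 = 0.96. Rejection is 5-6%, so there is almost no inflation.

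A second grid, with severity in 20-30% of DZHJTI patients against 30-40% of controls and g from 1.5 to 3, gives ratios from 1.40/1.80 = 0.78 to 1.15/1.20 = 0.96.

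None of these shares, hazard multipliers or event counts comes from the document. The direction is assumed too: if DZHJTI went to sicker patients, the ratio would exceed 1.

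**3. Competing deaths.**

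- Overall mortality: no competing event, so Kaplan-Meier is suitable.
- Stroke recurrence: any death that is not itself a recurrence competes.
- Major vascular events: Table 2 counts vascular-related death as a component, so only non-vascular death competes.

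With constant hazards λ1 for the event and λ2 for competing death over time t:

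- 1 − KM = 1 − exp(−λ1t)
- true cumulative incidence = [λ1/(λ1 + λ2)] × [1 − exp(−(λ1 + λ2)t)]

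For small hazards the ratio of the first to the second is about 1 + λ2t/2. The relative overstatement is therefore roughly half the 6-month cumulative hazard of competing death. The document gives no mortality figure to put in. Over 6 months the overstatement is probably modest, and it is smaller for the vascular composite than for recurrence if the event hazards are similar, because fewer deaths compete.

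**The case against.** The strongest reply is that the article nowhere calls these analyses crude. Cox is a regression method that normally takes covariates. The second paragraph says that confounding will be taken into account in the data analysis and does not confine AIPW to the primary outcome. The Discussion offers AIPW as the general answer to differences between sites and co-treatments, and the pseudopopulation wording is compatible with weighted curves. Covariates, weights and variance estimators are usually left to the statistical analysis plan, which exists. The illustrations above presuppose no adjustment at all, which is the very thing in doubt.

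Much of this stands. A reader might infer that crude comparisons are planned, or that the event results are bound to be confounded. The text supports neither inference. The absence of a Cox covariate list is not a fault in a condensed article.

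Two things remain. First, the mismatch lies in what the article states: it names two quantities for event outcomes and a remedy that produces neither. Assuming that the unseen plan adds covariates to the Cox model does not resolve this, because a covariate-adjusted hazard ratio is conditional and the article says it wants a marginal estimate. Second, Kaplan-Meier for cumulative events is a stated choice of method, not an omission.

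On competing deaths, it is fair to reply that a cause-specific Cox hazard ratio remains interpretable, that several serious comorbidities are excluded, and that follow-up is short. These limit the size of the problem, but do not make one minus Kaplan-Meier the right estimate of cumulative incidence.

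**Conclusion.** The point holds in a limited form. The article links no confounding adjustment to the Kaplan-Meier and Cox analyses of physician-selected groups, and the adjustment it does name does not itself yield those quantities. If the analyses are run as the sentences stand, the comparisons of mortality, recurrence and vascular events would carry confounding by indication. It is not established that they will be run that way.

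The size cannot be derived from the document. On assumed inputs with no adjustment, the distortion ranges from negligible (ratio 0.96, type I error 5-6%) to material (ratio 0.84, type I error 14-23%; ratios down to 0.78 on the wider grid).

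The Kaplan-Meier choice overstates the cumulative incidence of recurrence and of the vascular composite when competing deaths are censored, probably modestly. Overall mortality is not affected by that part. Both parts concern secondary outcomes only; the primary NIHSS outcome is untouched. The change is worth making because it is cheap and uses data already collected.

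**What to change.** Add two or three sentences to Statistical Analysis, or confirm that the statistical analysis plan contains them:

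- The propensity model is also applied to the event outcomes. Use either weighted cumulative incidence curves and a weighted Cox model with robust or bootstrap variance, or AIPW estimates of 6-month risk in each group. Say which of these carries the inference.
- Cumulative incidence of stroke recurrence and of major vascular events is estimated by Aalen-Johansen (weighted, as above), with death from any cause competing for recurrence and non-vascular death competing for the composite. Kaplan-Meier, likewise weighted, stays for overall mortality.
- Any unadjusted Kaplan-Meier, Cox, t, chi-square or rank comparison of outcomes is labelled descriptive.

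The cost is some extra programming and possibly slightly wider intervals than the unadjusted ones. No new data and no change to recruitment are needed.

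### The exclusion for other dosage forms of Dazhu hongjingtian (DZHJT) applies to controls only, so the planned contrast is not that of the injection alone

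*Protocol article*

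**What the plan says.** Four parts of the protocol article bear on this.

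- **Textbox 1, exclusion criteria.** The criterion on other dosage forms of DZHJT (tablets, capsules and the like) names controls only. No other criterion removes DZHJTI recipients who took the same products.
- **Treatment Regimens.** The exposed group is defined by receipt of the injection alone: "Cases will be recruited from patients who receive DZHJTI according to the physician’s order". The usual background treatments include "medicines for improving cerebral blood flow, and traditional Chinese medicine", so nothing bars oral DZHJT in that group. The Discussion adds that "the treatments will not be specified by the study protocol".
- **Objective and Conclusions (Abstract).** The effect to be evaluated, and later reported, is that of DZHJTI, the injection.
- **Statistical Analysis.** The augmented inverse propensity weighted (AIPW) "estimator will be used to obtain a marginal estimate of the treatment effect rather than a conditional estimate", with the stated justification that "AIPW analysis creates a pseudopopulation in which the relationship between the confounders and the exposure is blocked". For residual bias, "Sensitivity analyses for unmeasured confounding in observational studies will be performed using the methodology proposed by VanderWeele and Ding".

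**The concern.** Eligibility differs by exposure group on a variable that is close to the exposure itself. A patient who took DZHJT capsules is ineligible without the injection and eligible with it. Two consequences follow, depending on when the oral product was taken.

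- **Before treatment.** If prior oral use is related to prognosis, it is a confounder with no controls in one of its levels. AIPW cannot balance that level.
- **Alongside the injection.** Oral use is then a co-intervention allowed in one group and absent from the other.

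Either way, an effect of the oral product, or of the kind of patient who takes it, is credited to the injection. Enrolling more patients does not reduce this. Double robustness, which the Discussion cites in support of AIPW, does not help either, because it presupposes comparable patients in both groups.

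**Working it through.** The plan states no figure on this point, so there is nothing to reproduce. The check has a logical part and an illustrative part.

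**1. Overlap.** Let A = 1 for DZHJTI, X the covariates including prior oral use, e(X) the probability of DZHJTI given X, and m0(X) the outcome model fitted in controls. The AIPW estimate of the mean outcome without the injection averages

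m0(X) + (1 − A)(Y − m0(X)) / (1 − e(X)).

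Among enrolled oral users, A is always 1 under the Textbox 1 rule, so e(X) = 1.

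- The weight 1/(1 − e(X)) is undefined in that stratum.
- m0(X) is fitted on controls, none of whom is an oral user, so its value there is extrapolation.
- If oral use is left out of both models, the imbalance stays in the estimate.
- The planned sensitivity analysis addresses unmeasured confounding. It does not supply the missing controls.

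**2. Possible size.** Inputs from the Sample Size section:

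- ineffective rate in controls: 8.75% (7/80);
- ratio of cases to controls: 0.31, read here as a risk ratio and used as the strongest oral effect considered;
- 1000 per group with 20% dropout: 1000 × 0.80 = 800 evaluable per group.

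Assumptions, because the article gives no figures:

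- the injection has no effect;
- a share q of the DZHJTI group are oral users, q = 5%, 10%, 20% or 30%;
- oral users have a risk ratio r for an ineffective outcome, r = 0.31, 0.5 or 0.7;
- the analysis is approximated by an unweighted two-sided 5% test of two proportions.

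Rate in the DZHJTI group = 8.75% × (1 − q + q·r).

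Example, q = 20% and r = 0.31: 8.75% × (0.80 + 0.062) = 7.54%. The apparent ratio is 0.86 and the difference 1.21 percentage points. The standard error is √[(0.0875 × 0.9125 + 0.0754 × 0.9246)/800] = 0.0137, so the expected z is 0.0121/0.0137 = 0.88. The two-sided rejection probability is 14.3%.

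Apparent risk ratio and, after the semicolon, rejection probability under a null injection effect:

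| Oral use q | r = 0.31 | r = 0.5 | r = 0.7 |
|---|---|---|---|
| 5% | 0.97; 5.5% | 0.98; 5.3% | 0.99; 5.1% |
| 10% | 0.93; 7.2% | 0.95; 6.1% | 0.97; 5.4% |
| 20% | 0.86; 14.3% | 0.90; 9.7% | 0.94; 6.6% |
| 30% | 0.79; 27% | 0.85; 16.1% | 0.91; 8.8% |

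With q = 0, or with the same rule in both groups, the spurious difference from prior oral use is zero and the rejection probability is 5%.

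**The case against.** **The contrast may be intended.** Keeping controls free of the same herb avoids contamination, and the injection as used in practice against no DZHJT is a legitimate pragmatic comparison. This stands in part: the contrast can be defended if it is named. The article does not name it and attributes the result to the injection.

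**Oral users may hardly exist in the DZHJTI group.** This stands. Nothing in the article shows that any DZHJTI patient takes an oral product; traditional Chinese medicine is mentioned only in general. The overlap failure depends on such patients being enrolled and on their use preceding treatment.

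**The Statistical Analysis Plan may deal with it.** The quoted AIPW sentence is a general description of weighting, and the article does not list the covariates. An unseen plan could restrict the analysis population, which is the remedy proposed below. A covariate list alone could not help, because eligibility has already removed the controls who would be needed.

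**The 0.31 scenario is extreme.** It gives an oral product the full ratio quoted for DZHJTI while the injection does nothing. This stands, which is why the table also shows weaker effects.

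A reader might also infer two stronger points that the document does not support.

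- **Controls dropped for capsule use after enrolment**, which would inflate control mortality. The criterion gives no time window, but the Participants section applies the criteria at eligibility screening, and Table 1 places that screening at admission only. No later removal is described.
- **A contradiction with the Discussion**, which says "This approach has the advantage of reflecting real-world clinical practice, including therapy switches and concomitant medications". That is a general remark on observational designs. It would conflict with the criterion only if controls were removed for later switches.

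**Conclusion.** The point holds in a limited form. The criterion is asymmetric as written, and no other section of the article offsets it. The estimated quantity is therefore injection with or without oral DZHJT against no DZHJT of any form, while the stated aim is the effect of the injection. If prior oral users are enrolled and their use is related to prognosis, AIPW can only extrapolate for them. If the use is concurrent, it is a co-intervention in one group.

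The size cannot be determined from the document. Under the assumptions above, the distortion is negligible at 5% oral use whatever the effect. It stays small at 10%, and becomes material only when oral use is common and its effect strong: 27% rejection at 30% use with r = 0.31, but 8.8% with r = 0.7. This is an inexpensive improvement to consider. It does not show that the study's result will be biased.

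**What to change.** 1. Reword the Textbox 1 criterion so that prior use of other DZHJT dosage forms is treated alike in both groups, and state that it is assessed at admission screening.
2. Recruitment began in November 2022, so a reworded criterion cannot reach patients already enrolled. For them, restrict the main AIPW analysis to patients without recorded prior oral DZHJT use, where the records allow.
3. Report the unrestricted result as a sensitivity analysis, labelled as injection with or without oral DZHJT versus no DZHJT.

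**Cost.** One reworded criterion, one sentence on the analysis population, and a check of prior oral use in the DZHJTI group. Some DZHJTI patients are lost, against a planned 1000 per group where the plan states that 619 are required. The check may be incomplete: the Data Collection and Monitoring section takes medical history from the records but names no field for prior oral DZHJT. The number of patients whose prior use cannot be established should therefore be reported.
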